### Statistical analyses, power and sample size calculation

The prognostic capacity of the initial series of tests (physical examination of the cervical spine and QST) will be calculated by means of a logistic regression analysis, comparing the results of the responders with those of the non-responders. Instead of starting with a full regression model, two known prognostic factors, derived from the study from Jull and Stanton [8] will be included in the analysis a priori. Those two factors are 'light-headedness' and 'joint pain on palpation'. Consequently a backwards stepwise selection will be used, including the two known factors in the smaller models. Differences at baseline between the two treatment groups will be included in the regression models as potential prognostic factors. The plausibility of the signs will be considered to check the logical contribution of each factor in the model. The power of the obtained models will be analysed via the area under the ROC-curve.

Group differences and effect sizes can be calculated for headache intensity and frequency, medication intake, HIT-6 scores and absenteeism. The number of responders and non-responders in both groups will be compared. GPE is a dichotomous variable. Sample size calculations with a significance level of p < 0.05, an event rate of 0.50 in the usual care group and of 0.70 in the usual care plus musculoskeletal physiotherapy group a power of 80% and an equal amount of subjects in both treatment groups result in a sample size of 93 subjects in each treatment group. This results in a total of 186 subjects.

The results of all subjects will be analysed, regardless of their treatment adherence (intention-to-treat analysis).

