## Abstract

**Background:**

Treatment of headache disorders is not always optimal. Patients are treated in multiple ways, and the lack of scientific arguments for referral and the insufficient implementation of guidelines result in unclear treatment strategies.

The coexistence of headache and neck pain can lead to the referral to a musculoskeletal physiotherapist. This treatment can only be successful if an underlying cervical segmental dysfunction is present. In such cases a physical treatment can be a valuable option that should be considered.

The aim of this study is to identify prognostic therapeutic patient characteristics and to increase the number of correct physiotherapy referrals.

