These therapeutic uncertainties contribute to patients' treatment dissatisfaction. Relatively high percentages of headache sufferers are not satisfied with the headache care they receive. Harpole and co-workers investigated the headache burden and patient satisfaction with existing management in primary care, using patient-administered surveys. Of the 385 responders, who all contacted a GP because of their headache, 48 % reported problems with headache management and 17 % were dissatisfied with the headache care. Patients with a high headache-related impairment reported more problems with their headache management [20]. Walling et al. found that 26 % were dissatisfied in their sample of 447 migraine patients [21].

The prevalence and burden of headache, the dissatisfaction percentages and the diversity in headache treatments, call for a refinement of headache management.

The identification prior to the start of a treatment, of patients whom might react properly to the treatment, is necessary to reduce the risk of a negative outcome. For this purpose, patient characteristics which predict the treatment outcome (prognostic characteristics) need to be determined.

Prognostic factors are multifactorial. Jull and Stanton analysed the results of 152 CErvicogenic Headache (CEH) patients who participated in one of the three active treatment groups in a headache trial [9]. The prognostic value of socio-demographic factors, headache features, physical impairments of the cervical spine, neck pain and disability and patients' perceptions of influences on their headaches (locus of control) was investigated. They were unable to identify a systematic pattern of prognostic factors. Only the presence of light-headedness appeared to be a clinically relevant predictor of a bad outcome. Of the physical tests only joint pain on palpation had a prognostic value [22]. Of their tests only this palpation could be used for prognostic uses.

Our study has a double aim. Our primary aim is to analyse the prognostic value of a series of physical tests. Our secondary aim is to compare two currently applied treatment strategies, being the usual care (UC) administered by a medical doctor following a stepped guideline [7], and the UC plus a musculoskeletal physiotherapy treatment protocol (UCMT), described by Jull et al [9].

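### The prognostic regression, as described, names no treatment arm and no arm-by-test interaction, so it can serve general prognosis but cannot support the aim of better physiotherapy referral

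*Protocol article*

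**What the plan says.** The Abstract (Background) gives the aim as "to identify prognostic therapeutic patient characteristics and to increase the number of correct physiotherapy referrals". The Background section adds that "patient characteristics which predict the treatment outcome (prognostic characteristics) need to be determined", so that likely responders to a treatment can be recognised before it starts. The same section then states the primary aim more narrowly: "Our primary aim is to analyse the prognostic value of a series of physical tests". The added value of physiotherapy is the secondary aim.

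The section on statistical analyses, power and sample size describes the prognostic model as a logistic regression "comparing the results of the responders with those of the non-responders". Its stated contents are:

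- the cervical examination and the quantitative sensory tests;
- two factors from an earlier prognostic analysis (light-headedness and joint pain on palpation), kept throughout a backward selection;
- covariates chosen by comparing the arms: "Differences at baseline between the two treatment groups will be included in the regression models as potential prognostic factors".

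Model performance is judged by the area under the ROC curve. The arms are compared on response only in a separate count of responders and non-responders, and the sample size of 93 per arm is set for that comparison.

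**The concern.** Whether a patient should be referred to physiotherapy depends on how much adding it improves that patient's chance of response. This is a difference between UCMT and UC at a given test result, and in a regression it appears as an arm-by-test interaction. A main effect estimated across both arms answers another question: whether test-positive patients do better on average, whatever they receive.

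The two can diverge in either direction. A test that predicts a good outcome equally under UC and UCMT would be reported as a finding although it carries no referral information. A test that truly separates those who benefit can be diluted by the UC patients, or cancelled altogether. The trial randomises between exactly the two strategies that matter for referral, yet the model as described does not use that contrast. At stake is referral advice resting on tests that do not distinguish who benefits.

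**Working it through.** **Inputs from the Protocol article (statistical section).** Response 0.50 in UC and 0.70 in UCMT, significance level 0.05, power 80%, equal arms, 93 per arm, 186 in total.

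**The plan's own figure.** Two-sided test of two proportions, pooled variance, no continuity correction:

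n = [1.960·√(2·0.60·0.40) + 0.8416·√(0.50·0.50 + 0.70·0.30)]² / 0.20² = (1.358 + 0.571)² / 0.04 ≈ 93 per arm.

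The stated figure is reproduced. At these rates 93·0.50 + 93·0.70 = 111.6, so about 112 responders and 74 non-responders enter the regression. Of the responders, 65 come from UCMT and 46.5 from UC. By the plan's own assumption, response depends on an arm that the model does not name.

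**Assumptions, not in the documents.** One binary test, positive in 50% of each arm. Response rates by test result are chosen so that the arm averages stay at 0.50 and 0.70.

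**What a pooled model sees.** The pooled rate in each test group is the mean of the two arm rates, and the pooled odds ratio (OR) is the ratio of the resulting odds.

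| Pattern | UCMT test+ / test− | UC test+ / test− | Gain test+ / test− (points) | Pooled rates | Pooled OR |
|---|---|---|---|---|---|
| A. Marks who benefits | 0.90 / 0.50 | 0.50 / 0.50 | 40 / 0 | 0.70 / 0.50 | (0.70/0.30)/(0.50/0.50) = 2.33 |
| B. Prognostic only | 0.80 / 0.60 | 0.60 / 0.40 | 20 / 20 | 0.70 / 0.50 | 2.33 |
| C. Crossover | 0.80 / 0.60 | 0.40 / 0.60 | 40 / 0 | 0.60 / 0.60 | 1.00 |

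A and B give identical pooled data and are each significant about 79% of the time. Only A would justify selective referral. C would justify it as much as A, but shows no pooled association and would tend to leave the model in backward selection.

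**What an interaction test sees.** Wald test of the log ratio of odds ratios, b, with variance Σ 1/[n·p·(1−p)] over the four arm-by-test cells, n = 93/2 = 46.5 per cell, and power = Φ(|b|/SE − 1.960). UC is 0.50 in both test groups:

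- UCMT 0.80 / 0.60 (gain 30 versus 10 points): b = ln 2.67 = 0.981, SE = 0.629, power 34%. About 601 patients in total would be needed for 80%.
- UCMT 0.85 / 0.55 (35 versus 5): b = ln 4.64 = 1.534, SE = 0.654, power 65%. About 266 patients would be needed.
- UCMT 0.90 / 0.50 (40 versus 0, pattern A): b = ln 9 = 2.197, SE = 0.705, power 88%.

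Simulation with 46 patients per cell gives much the same: about 33–34%, 65–66% and 90–91%. In simulation the interaction test rejects in about 5–6% of trials under pattern B and about 81–82% under pattern C, so it separates all three patterns. In B the equal gain of 20 points corresponds to a ratio of odds ratios of 2.67/2.25 = 1.19 rather than exactly 1. This is a reason to report differences in response rate alongside the interaction term.

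**The case against.** **The declared primary aim is prognosis.** The Background section and the first research question ask for prognostic characteristics. A regression of responders against non-responders with a ROC area is a legitimate method for that. This stands. A reader might infer that the primary analysis fails; the documents do not support that. The mismatch is with the referral aim in the Abstract.

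**Pooling is not stated.** No sentence says that the arms are combined, and the text speaks of regression models in the plural. This also stands: pooling is inferred. It is nevertheless the natural reading, because the contrast names no arm and differences between arms enter as covariates. The remark on pooling in the Discussion concerns centres. Separate models per arm would still need a formal comparison between arms before they could inform referral.

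**The article is condensed.** A covariate list may be left to an analysis plan. But this article does set out the forced terms, the candidates, the selection method and how between-arm differences enter. The point rests on what it describes, not on missing detail.

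**The hypothesis.** A reader might take the statement "This treatment can only be successful if an underlying cervical segmental dysfunction is present" as a hypothesis of effect modification under test. It is background rationale, and no analysis is tied to it.

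**Baseline imbalance.** A reader might infer that adding unbalanced characteristics while omitting arm produces many false prognostic factors. The design does not bear this out. Allocation is randomised in blocks of ten within diagnosis. With 93 per arm, a 60/40 split on a given factor present in half the patients has a probability of about 0.006, and 65/35 or 70/30 practically never occurs. Averaged over randomisation, omitting arm gives a rejection rate of about 4.8%, so there is no inflation.

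**Power.** Interactions at 186 patients will often be inconclusive. This is true, and it is why they should be labelled exploratory.

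**Conclusion.** The concern holds in a limited form. As described, the regression can identify characteristics associated with response in general, but it cannot show whom to refer to physiotherapy. Under the assumed 50% test prevalence and the planned arm averages, tests with opposite implications for referral share a pooled odds ratio of 2.33, and one informative test has a pooled odds ratio of 1.00. The conclusion rests on reading the model as pooled. The size of the effect rests on the assumed response rates, which are illustrations and not forecasts. The randomised comparison of response and its sample size are unaffected. This should be fixed, because without the change the referral aim has no analysis behind it.

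**What to change.** - Force treatment arm into every regression model. This is necessary but not sufficient, since an arm term alone does not estimate who benefits.
- Pre-specify arm-by-test interactions for a few hypothesis-driven tests, for example one rotation-test score, one pain-provocation score and one or two sensitisation scores.
- Report the UCMT–UC difference in response, with its interval, in test-positive and test-negative patients.
- Describe main effects as prognostic only. Base any statement about referral on the interactions, and label those exploratory.

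The cost is a change of analysis wording, with no new data or patients. The downside is a few more parameters and wide intervals: unless effect modification is very large, 186 patients will leave the interactions imprecise. If the referral claim is meant to be confirmatory, the trial would have to be sized for it.

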##### Thermal and pressure stimuli

Thermal and pressure stimuli are used to detect sensitisation. Stimuli are applied in cranial and extra-cranial regions. To screen for central sensitization, measurements were also taken on the dorsal side of the index, on the tibialis anterior (pressure) and on the thenar (temperature).

Thermal stimuli will be investigated using the TSA II Thermotest (Medoc Advanced Medical Systems Ltd. [name]). A thermode of 30 × 30 mm is attached first to the skin of the hand (palmar thenar, C6), next to the mastoid process (C2) and finally to the temple (trigeminal nerve). Starting from a baseline temperature of 32°C, the intensity of the stimulus will vary following the method of limits protocol (+/- 1°C/s). Four modalities are tested: cold and warm sensation (CS and WS) and cold and heat pain detection thresholds (CP and HP). First subjects are asked to press a button as soon a change in temperature is perceived (CS and WS, 4 stimuli). Second they have to push the button when the temperature stimulus is perceived as unpleasant/painful (CP and HP, 3 stimuli). All measurements are performed bilaterally. The average of the repetitions is used for further calculations.

The sequence of the thermal stimuli is chosen to familiarise the subjects with the test: it is reassuring to have the first set of stimuli on the hand and not on the head, which is the site of the complaints. This method has been shown to be reliable [36].

Pressure stimuli are measured using a hand held algometer (Somedic AB, Farsta, Sweden). Pain detection thresholds will be measured on the temple, the mastoid process, the dorsal side of the index and on the tibialis anterior muscle. The average of three measurements will be used for further calculations. Subjects have to report when the feeling of pressure alone changes into a feeling of pressure and pain.

Quantitative Sensory Tests are psychophysical tests. To increase the reliability and ecological validity of the tests, all measurements will be performed at the participants' home.

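### Backward selection over an unfixed set of roughly 19 to 50 test results, with about 74 non-responders, is very likely to keep worthless tests and to overstate the AUC for the primary aim

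*Protocol article*

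**What the plan says.** The Background section ranks the aims: "Our primary aim is to analyse the prognostic value of a series of physical tests". Comparing usual care with usual care plus physiotherapy is the secondary aim. The Discussion in the Abstract presents the intended product as a diagnostic tool for everyone who treats headache.

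The section on statistical analyses, power and sample size takes as predictors "The prognostic capacity of the initial series of tests (physical examination of the cervical spine and QST"), with responder status on the global perceived effect as outcome. Two factors from an earlier study are forced in. The selection step reads: "Consequently a backwards stepwise selection will be used, including the two known factors in the smaller models". Baseline differences between the arms enter as further candidates, the plausibility of the signs is considered, and performance is assessed as follows: "The power of the obtained models will be analysed via the area under the ROC-curve".

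The same section contains the only sample size calculation. It compares responder rates of 0.50 and 0.70 between the arms and gives 93 per arm, 186 in total.

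**The concern.** Stepwise selection over many candidates with few outcome events tends to keep predictors by chance. An AUC computed in the patients used for selection then counts that chance fit as discrimination. The number of patients was set by a different question, and nothing sizes the prognostic model.

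This affects the primary result. If the tests carry little information, the plan would still probably deliver a model with named tests and a respectable-looking AUC, and that model is meant to guide referral. A weak truth is not far-fetched: the Background section reports that an earlier analysis of 152 cervicogenic headache patients found no systematic pattern of prognostic factors, and only one physical test with prognostic value.

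**Working it through.** **1. The plan's own figure.** Two proportions, 0.50 and 0.70, two-sided alpha 0.05 (sidedness is not stated, but two-sided reproduces the figure), power 80%, pooled variance under the null, no continuity correction:

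n = [1.960 × √(2 × 0.60 × 0.40) + 0.842 × √(0.50 × 0.50 + 0.70 × 0.30)]² / 0.20² = (1.358 + 0.571)² / 0.04 ≈ 93 per arm.

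This reproduces 93 per arm and 186 in total. It serves the treatment comparison only.

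**2. Size of the smaller outcome class.** Non-responders: 93 × 0.50 + 93 × 0.30 = 74.4. Responders: 186 − 74.4 = 111.6. Non-responders are the limiting class. No dropout is deducted.

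**3. Candidate count** (from the sections on the physical examination of the cervical spine and on thermal and pressure stimuli).
- Thermal: "Four modalities are tested: cold and warm sensation (CS and WS) and cold and heat pain detection thresholds (CP and HP"), on the hand, "next to the mastoid process (C2) and finally to the temple (trigeminal nerve"), and "All measurements are performed bilaterally". So 4 modalities × 3 sites × 2 sides = 24.
- Pressure: 4 sites (8 if bilateral, which is not stated for pressure).
- Rotation test: 2 directions × 2 regions = 4.
- Pain provocation test: 7 segments, C0-1 to C6-7 (14 if both sides are recorded separately).

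Entered one by one: 24 + 4 + 4 + 7 = 39. With bilateral pressure and provocation: 24 + 8 + 4 + 14 = 50. With thermal sides averaged: 12 + 4 + 4 + 7 = 27. Collapsing further, for example rotation by region and provocation as one result: 12 + 4 + 2 + 1 = 19. The two forced factors and any baseline differences come on top.

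**4. Quick check.** For k independent worthless tests, P(at least one p<0.05) = 1 − 0.95^k. With k = 39 this is 0.865; at 0.10 it is 1 − 0.90^39 = 0.984.

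**5. Null simulation.** Assumptions not in the documents: removal at p>0.05 or p>0.10, correlation within blocks of tests of 0 or 0.5, 35% positivity of the manual tests, both forced factors without effect, no dropout. Each trial has 186 patients with responder rates 0.50 and 0.70, backward Wald elimination with the forced factors retained, and the final model re-scored in 2,000 new patients. Ranges span the correlation settings and repeated simulations.

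| Candidates | Non-responders per candidate | Any worthless test kept, p>0.05 | Mean apparent AUC | Any kept, p>0.10 | Mean apparent AUC |
|---|---|---|---|---|---|
| 19 | 74.4/19 = 3.9 | 61–67% | 0.60–0.61 | 86–89% | 0.63–0.64 |
| 27 | 74.4/27 = 2.8 | 74–77% | 0.62–0.63 | 96% | 0.66 |
| 39 | 74.4/39 = 1.9 | 85–91% | 0.65–0.66 | 99% | 0.70 |
| 50 | 74.4/50 = 1.5 | 91–94% | 0.67–0.68 | over 99% | 0.73 |

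The AUC in new patients is 0.50 in every row. With 39 candidates the apparent AUC reaches 0.70 or more in 21–27% of null trials at 0.05 and in 49–54% at 0.10. The two forced factors alone, with no effect, give an apparent AUC of 0.55.

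**6. Sign check applied strictly.** If every wrong-signed test were deleted and the selection rerun, some worthless test would still be kept, with 39 candidates, in 42–60% of trials at 0.05 and 62–83% at 0.10. With 19 candidates at 0.05 it would be 25–35%.

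**The case against.** Several stronger readings are tempting, and the document does not support them.

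- *That 39 is a minimum.* It counts recorded results. The article never says that each becomes its own model term, and its per-test positivity rules fit a collapsed coding just as well. The honest statement is a range of about 19 to 50.
- *That a false model is certain.* Even with 39 candidates a null trial sometimes keeps no test, and the planned look at the signs could remove more. As written, however, the look at signs is a judgement with no stated directions and no deletion rule, so its effect cannot be counted on.
- *That the plan contradicts itself.* Backward elimination normally starts from a full model, yet the text begins "Instead of starting with a full regression model, two known prognostic factors". A coherent reading exists: the two known factors are exempt from removal and the rest are eliminated backward. The wording needs clarifying but is not an error in itself.
- *That the AUC will certainly go uncorrected.* The article names no correction and no second data set. An analysis plan not shown here could add internal validation. That would repair the reported AUC. It would not stop chance selection or add non-responders.
- *That the tests selected here will be mostly chance.* The simulation shows this only when nothing predicts. The article gives some prior grounds for signal, and no partial-signal scenario was run. Some of the apparent AUC also comes from fitting the forced factors, not from selection.

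What stands of the objection is that the size depends on coding and thresholds the article does not fix. What falls is the idea that favourable coding rescues the plan: 19 candidates still give false retention in about six of ten null trials.

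**Conclusion.** The point holds as a badly chosen method for the primary aim, not as a missing detail: backward selection, open-ended extra candidates and the AUC are all stated choices. With about 74 non-responders and 19 to 50 candidates, a trial in which no test has value would keep at least one in roughly 61–94% of cases at p>0.05. The apparent AUC would exceed the true value by about 0.10 to 0.18 on average (0.60–0.68 against 0.50), and by more at p>0.10. A strict sign rule lowers the retention rate without solving the problem.

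These figures rest on the planned responder rates, full follow-up, one model over both arms, and the assumed thresholds and correlations. Dropout, or fitting within one arm (93 × 0.30 ≈ 28 non-responders in the physiotherapy arm), would make matters worse.

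**What to change.** Before outcome data are examined:

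- Specify a short list of summary predictors, each with its coding over sides, regions and segments and its expected sign. Which summaries to use is for the investigators to decide.
- Fit them together with the two forced factors and treatment arm, by penalised logistic regression or a full model with shrinkage, in place of stepwise selection. Shortening the list is not enough: with 6 worthless summaries and selection at p<0.05, at least one was still kept in 27% of simulated trials (mean apparent AUC 0.57).
- Report a bootstrap optimism-corrected AUC, with every modelling step repeated in each bootstrap sample, together with calibration.
- State that 186 was sized for the treatment comparison, and that the prognostic model is exploratory until validated in other patients.
- Reword the sentence about not starting from a full model so that the starting model is clear.

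The cost is analysis wording and some computing, with no extra patients or measurements. The downside is less anatomical detail and a lower reported AUC.

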### Patients selection

Using a multicenter setup, patients will be recruited at GPs offices, from outpatient clinics of the neurology department of the academic hospitals UZ Brussel and UZA and via advertisements.

All participating medical doctors (GP's and neurologists) were contacted and personally informed about the study protocol. Additional information is provided on an informative website [23].

The advertisements contain a weblink to an informative recruitment website [24]. On this site detailed information is provided, followed by an online eligibility screenings procedure.

Different recruitment strategies can result in a heterogenous study population. This will not necessarily affect treatment outcome [25]. Subgroups will be compared at baseline. In case differences are found these will be taken into account in the statistical analysis (see section 'Analyses').

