### Follow-up measurements

After approximately 7, 12, 26 and 52 weeks, participants will be asked to complete the Headache Inventory List and HIT-6 again. For all questionnaires a recall period of four weeks is chosen, in correspondence with the recall period of the HIT-6.

The global perceived effect (GPE) is measured using a 7 point scale, ranging from 'completely recovered' to 'worse than ever'. This way of measuring GPE has been used in similar studies in which the effect of commonly applied therapeutic approaches have been compared [37,38]. Responders (positive effect) and non-responders (no effect or worse) can be identified.

The follow-up measurements are also available online ensuring a blinded rater assessment. The questionnaires which are returned in paper version (from participants without internet connection) will be inserted in the software by an independent blinded rater.

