#### Primary and secondary outcome measures

Two primary outcome measures will be used in this study: GPE and the HIT-6 score.

Reduction in headache frequency, headache pain intensity, medication intake, absenteeism and looking for professional help will be used as secondary outcome measures.

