### Randomisation

After baseline measurements patients are randomised. Subjects are randomised using blinded envelopes, using a pre-stratification for the headache diagnosis. So, an envelope for migraine, tension-type headache and CEH is provided. Each envelope contains 10 notes, five mentioning usual care and five mentioning usual care plus manual therapy. This to ensure that for each 10 patients with the same diagnosis, the same number of patients is randomised in one of the two treatment groups. Due to the randomisation after testing all tests are performed by a blinded rater.

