We preferred not to include generic questionnaires like the SF-36 in our outcome measures. This was mostly out of practical considerations: the initial set of questionnaires is quite long to complete. Adding another questionnaire can discourage patients to participate. The influence of migraine, tension-type headache and CEH on Quality Of Life (QOL) has been investigated before [41].

Quantitative Sensory Testing using thermal and pressure stimuli have been used to study patho-physiological mechanisms in headache patients [42-46]. General hypersensitivity has been demonstrated to be present in Whiplash patients with moderate to severe symptoms and not in recovered patients or those with mild symptoms [47]. This indicates the potential value of this test in predicting the evolution of a disorder.

The number of participants is the weak point of every clinical study. A pilot running from February 06 to June 06, with only first line recruitments resulted in 15 referred patients. To obtain the required number of patients the way of recruitment was adapted. Second line and advertisement recruitments were also included. The results will be analysed as in any multicenter trial: intercenter differences will be analysed to verify if patients can be pooled.

No training sessions dealing with the study protocol or treatments were organised for the participating medical doctors or therapists. This is a potential weakness of the study protocol. It was impossible to organize these sessions. The referring doctors receive no financial incentives or compensations whatsoever for participation in this study. They participate out of goodwill. Additional time investments would decrease this goodwill. We tried to have their commitment by informing them personally and by providing additional information on a website developed for that purpose [23].

The therapists could not be trained in advance either as it is not known in advance which therapists will participate. This depends on the patient's residence. Therefore the letter with treatment recommendations is provided.

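### Observed differences between arms, recruitment routes and centres decide what enters the models and whether patients are pooled; these terms should be fixed in advance

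*Protocol article*

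**What the plan says.** Three statements in the protocol article make the analysis depend on what is observed.

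- Statistical analyses, power and sample size calculation: "Differences at baseline between the two treatment groups will be included in the regression models as potential prognostic factors". The sentence stands in the paragraph on the logistic regression of responders against non-responders, next to the backward selection. Only two factors are fixed in advance there: light-headedness and joint pain on palpation.
- Patients selection, on the different recruitment routes: "In case differences are found these will be taken into account in the statistical analysis". The reader is pointed to the analysis section, which has no rule for recruitment route.
- Discussion, on the multicentre design: "intercenter differences will be analysed to verify if patients can be pooled". Neither a criterion nor a consequence is given.

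Four other statements bear on the remedy. Randomisation is done "using a pre-stratification for the headache diagnosis", with ten notes per envelope, five for each arm. The outcomes section says: "Two primary outcome measures will be used in this study: GPE and the HIT-6 score". HIT-6 is taken at baseline, and at about 7, 12, 26 and 52 weeks "participants will be asked to complete the Headache Inventory List and HIT-6 again". For the treatment comparison the analysis section offers: "Group differences and effect sizes can be calculated for headache intensity and frequency, medication intake, HIT-6 scores and absenteeism", plus a comparison of responder counts. It names no model and no covariates.

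**The concern.** In a randomised trial, a baseline difference between arms is a chance event. It carries no information on whether a variable predicts response. Using it to nominate prognostic factors brings in variables for a reason unrelated to prognosis. It gives no place to a strong predictor that happens to be balanced, unless that predictor is already one of the physical or sensory tests or one of the two prior factors. This touches the primary aim, which is to find prognostic characteristics.

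The route and centre rules are a different matter. Those groups are not randomised, so differences between them may be real. But a term that enters only when a difference is noticed makes the model depend on one look at the data. A pooling check with no criterion and no alternative leaves open what is analysed if it fails.

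What is at stake is a prognostic model, and possibly an analysis population, that would have been specified differently under another chance allocation.

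**Working it through.** **1. The plan's own figure.** Inputs from the analysis section: response 0.50 and 0.70, significance level 0.05 (two-sided assumed), power 80%, equal arms. With mean proportion 0.60:

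n = [1.960 × √(2 × 0.60 × 0.40) + 0.842 × √(0.50 × 0.50 + 0.70 × 0.30)]² / 0.20² = (1.358 + 0.571)² / 0.04 = 93 per arm, 186 in total.

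This reproduces the article and does not depend on the present point.

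**2. How often chance would enter the prognostic model.** The article names no threshold. Assume a 5% level and k independent baseline variables. The probability that at least one is flagged under correct randomisation is 1 − 0.95^k:

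| k | 5 | 10 | 15 | 20 |
|---|---|---|---|---|
| Probability | 23% | 40% | 54% | 64% |

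The baseline set is long (a 56-item questionnaire, HIT-6, the inventory list, thermal and pressure thresholds at several sites), but many of its items are correlated, so these percentages are illustrative. A flagged variable would also still have to survive any backward selection applied to it.

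**3. Which variable the rule is least likely to admit.** With envelopes of five and five, the arms can differ by at most 5 patients within a diagnosis, and only while an envelope is incomplete. Headache diagnosis is therefore balanced by design. A rule based on imbalance would hardly ever admit it, however prognostic it might be.

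**4. What fixed adjustment could bring to HIT-6.** The article gives neither a standard deviation nor a baseline to follow-up correlation ρ, so both are assumed. Relative to unadjusted follow-up scores, baseline adjustment multiplies the variance of the treatment effect by 1 − ρ². Relative to change scores, whose variance factor is 2(1 − ρ), the ratio is (1 − ρ²)/[2(1 − ρ)] = (1 + ρ)/2.

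| ρ | 1 − ρ² | Reduction against follow-up scores | Reduction against change scores |
|---|---|---|---|
| 0.3 | 0.91 | 9% | 35% |
| 0.5 | 0.75 | 25% | 25% |
| 0.6 | 0.64 | 36% | 20% |
| 0.7 | 0.51 | 49% | 15% |

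Example with the article's 3-point important difference, SD 8 (assumed) and 93 per arm: 3 / (8 × √(2/93)) = 2.557, and 2.557 − 1.960 = 0.597, so power is 0.725 unadjusted. Dividing 2.557 by √(1 − ρ²) gives power 0.764, 0.840, 0.892 and 0.947 at the four correlations. At ρ = 0.5, over SD 5 to 9, power runs from 0.983 down to 0.623 unadjusted and from 0.997 down to 0.747 adjusted.

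**5. What stratifying by diagnosis could bring to GPE.** The simulation used 40,000 trials per scenario and three equal diagnosis strata of 31 per arm (assumed). A common odds ratio was set so that overall response is 0.50 against 0.70. An unstratified test was compared with Cochran-Mantel-Haenszel (CMH).

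| Usual-care response by diagnosis (assumed) | Power, unstratified | Power, CMH | Type I error, unstratified |
|---|---|---|---|
| 0.5 / 0.5 / 0.5 | 0.799 | 0.795 | 0.048 |
| 0.4 / 0.5 / 0.6 | 0.804 | 0.812 | 0.044 |
| 0.3 / 0.5 / 0.7 | 0.810 | 0.838 | 0.035 |
| 0.2 / 0.5 / 0.8 | 0.827 | 0.889 | 0.023 |

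CMH kept its type I error between about 0.046 and 0.051. The gain runs from nil to about 6 power points. The unstratified test becomes conservative only where diagnosis is prognostic.

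**The case against.** The strongest reply is that the sentence on baseline differences belongs to the prognostic regression, while any loss of precision concerns the treatment comparison, which is the secondary aim. A reader might infer that arm imbalances set the covariates for that comparison, or that the plan ignores the stratification and baseline HIT-6. The document supports neither reading. For the treatment comparison it names no model, so adjustment is neither planned nor ruled out, and a full protocol or analysis plan may supply it. That silence is not the finding; diagnosis and baseline HIT-6 appear here only as part of the remedy.

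Other stronger readings fail as well.

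- Significance testing is not stated. The text speaks of comparing, analysing and finding differences.
- The number of sites is not given, so nothing can be said about many small centres.
- The HIT-6 threshold of 56 points applies only to internet and advertisement recruits. That makes a difference in baseline severity by route plausible; it does not show that route predicts outcome. The article itself says that mixed recruitment need not affect treatment outcome.
- For recruitment route a consequence is stated (differences are taken into account), though not how. Only the pooling rule has none.
- Leaving out diagnosis makes the unstratified GPE test conservative, so no excess of false positives follows.

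What remains is that the three rules are written down. A later analysis plan that elaborated them would still carry them.

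**Conclusion.** The point holds as one about data-dependent rules. Between-arm differences are a wrong criterion for nominating prognostic factors, and this affects the primary aim. Making the route term and the pooling decision conditional on observed differences is avoidable, and the pooling rule has no defined outcome if it fails.

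The size cannot be taken from the article. The 23% to 64% chance of admitting a spurious imbalance assumes a 5% threshold and 5 to 20 independent variables. The HIT-6 gain of 9% to 49% assumes correlations of 0.3 to 0.7 and unadjusted follow-up scores as the comparator; against change scores it is 20% at a correlation of 0.6. The GPE gain of roughly 0 to 6 power points assumes response rates by diagnosis that the article does not give, and it vanishes if diagnosis is not prognostic. These gains show what fixed adjustment could offer. They are not a demonstrated loss under the plan. The sample size is correct as stated.

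**What to change.** - **Prognostic model:** delete the rule on baseline differences between arms. List the candidate factors now, on prior clinical or published grounds, alongside the physical and sensory tests and the two factors already fixed.
- **Pooling and route:** pool all patients as planned. Include recruitment route (GP, neurology clinic, advertisement) as a fixed term whatever difference is observed, and report results by route descriptively. Remove the condition on pooling.
- **Treatment comparisons:** adjust for headache diagnosis, the stratification factor. For HIT-6 and the other continuous outcomes, also adjust for their own baseline value, by analysis of covariance or a mixed model. For GPE, use logistic regression with diagnosis and route.

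The cost is analysis wording only. Diagnosis, recruitment route and baseline HIT-6 are already known for each patient, and neither the sample size nor the data collection changes. The wording should be settled before outcome data are examined.
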